### Objectives

The purpose of this project is to increase our understanding of how to promote the well-being across a spectrum of outcome areas for youth (15 + years old) transitioning from out-of-home care to independent living through the study of the implementation and provision of (A) My Choice—My Way! (*Swe*. Mitt val–min väg!) and (B) Usual Services. This includes an increased understanding of how interventions for this population can be designed, implemented, and sustained in diverse settings.

The project has five specific aims and eleven research questions.

#### Aim 1

To test the short- and sustained effectiveness of My Choice-My Way! in normal practice settings.

H1: Youth participating in My Choice-My Way! will exhibit gains in well-being and psychosocial outcomes relative to youth participating in Usual Services.

*Research questions*. RQ1 What is the relative effectiveness of My Choice-My Way! and Usual Services (US) for youth aged 15 and older in out-of-home care on well-being and psychosocial outcomes?

RQ2 How are outcomes moderated by subgroup characteristics?

RQ3 How does implementation fidelity moderate outcomes?

RQ4 What is the relative economic impact of My Choice–My Way!?

#### Aim 2

To advance our understanding of how specific behavior change techniques and theory-based change mechanisms impact youth outcomes.

H2: Theoretically based change mechanisms (e.g., experiences of success targeting self-efficacy change) will have a mediating effect on outcome (e.g., increased engagement in educational activities) in interventions with detailed program content.

*Research questions*. RQ5 How are the specific behavior change techniques used by social workers related to theoretical change mechanisms?

RQ6 How do the specific change mechanisms in transition services mediate youth outcomes?

#### Aim 3

To assess the extent to which implementation support (i.e., GTO) can impact fidelity and sustainability in practice settings.

H3: Organizations engaging in implementation support will exhibit increased fidelity relative organizations not engaging in implementation support.H4: Organizations engaging in implementation support will exhibit increased sustainability relative organizations not engaging in implementation support.

*Research questions*. RQ7 How does implementation support impact fidelity?

RQ8 How does implementation support impact sustainability?

#### Aim 4

To increase our knowledge of the barriers and facilitators to implementing programs for youth in diverse contexts.

H: The following research questions are exploratory and hypothesis generating in nature.

*Research questions*. RQ9 What strategies were used (e.g., by social workers) to implement transition services (e.g., My Choice–My Way!) and how do these strategies compare and contrast to current implementation models and frameworks?

RQ10 What are the experiences of providers that have implemented My Choice–My Way! without systematic implementation support (i.e. GTO)?

#### Aim 5

To build knowledge of how youth experience participating in interventions designed to support them in the transition from out-of-home care to independent living.

H: The following research questions are exploratory and hypothesis generating in nature.

*Research questions*. RQ11 What is the participants level of satisfaction, acceptability and buy-in with the service in which they have participated?

### Trial design

The study can be described as a hybrid effectiveness-implementation study with natural controls in a quasi-experimental two-arm study design [30]. We will conduct such a study to test the impact of the leaving care interventions while we at the same time collect data on the implementation process and outcomes (i.e., Hybrid I design). Research design and methods for data analysis specifically linked to each of the aims and research questions will be described in more detail below.

#### Design Aim 1

We will perform an effectiveness study to achieve Aim 1 and to answer RQ1-RQ4. The effectiveness study will be carried out as a natural quasi-experiment with two groups of youth participants (My Choice–My Way!, US) with dependent pre-, post- and follow-up measures [31] (i.e., 3 x 3 mixed factorial design. Long-term outcomes will be studied with a longitudinal register study.

#### Design Aim 2

Based on the My Choice–My Way! theory of change (i.e., logic model, [32]) salient change mechanisms will be chosen and measured.

#### Design Aim 3

Posttest comparison study comparing implementation and youth level outcomes for organizations engaged in implementation support with organizations not receiving implementation support.

#### Design Aim 4

Qualitative implementation, posttest interview study with service providers.

#### Design Aim 5

Qualitative implementation, posttest interview study with youth participants.

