#### Project novelty

This project is novel in a number of ways. First, this project weaves together several complementary areas of research to meet the needs of the municipal social services and the youth in its care (i.e., implementation science, intervention science, developmental psychology, social work). Second, this research will experimentally test the effects of a locally developed, theoretically and empirically inspired intervention developed based on cutting-edge intervention development theory in collaboration with municipal stakeholders aiming to support an underserved and extremely vulnerable group, one of the municipal social services core populations. Third, this project will experimentally test the extent to which implementation support impacts fidelity, sustainability and client outcomes. Fourth, this research will increase our empirical understanding of how specific behavior change techniques (practice components) are related to theoretical change mechanisms (constructs) and how these constructs in turn are related to youth outcomes. This has the prospect of increasing our scientific knowledge of how intervention development and implementation can be approached in the future. Finally, there are currently no evidence-based and culturally sensitive interventions available to social service professionals for this population and purpose. Our work has the goal of developing our knowledge toward meeting this challenge.

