### Allocation

This study will follow the natural assignment of youth to condition (i.e., the research team will not manipulate the normal operating procedures of the participating municipalities/organizations but instead will follow youth as they are assigned to My Choice–My Way! and US). We will implement a rolling inclusion. Youth will be admitted to the study as they are referred to one of the study arms (My Choice–My Way!, US). Inclusion to the study will continue until we have included the desired number of participants.

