### Data collection methods

Youth level data will be collected through a digital questionnaire at three (i.e., T1, T2, T3) time points. First, pre-test measurements (T1), directly following the informed consent procedure but prior to program start. Post-test measurement (T2), after completion of My Choice–My Way! (approximately 8 months after T1, standardized across groups). Third, follow-up measurements (T3), 9 months following T2. Youth level register data will be collected 24 months after T1.

Upon declaration of interest to participate in the study, the youth will be given the option to give their informed consent and fill in the baseline questionnaire electronically via a link received through e-mail or over the phone with a member of the research team. Each youth who chooses to participate will receive compensation for their time upon filling out each questionnaire (approximately $20). Participants are able to choose between receiving compensation in cash or in the form of a gift card.

Service providers of My Choice—My Way! will be asked to complete a questionnaire post-T2 data collection investigating key determinants of implementation success.

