### Statistical methods

#### Aim 1 statistical methods

*Baseline characteristics*. Demographic/background and T1 values on outcome variables will be investigated for the entire group and each arm separately.

*Baseline differences in between-group analyses*. Baseline differences on background and outcome variables between groups at T1 (due to the absence of randomization) will be investigated (e.g., *x2*, *t*-test, Mann-Whitney U). Any identified differences will be statistically controlled for in between group analyses.

*Attrition*. Analysis of within group and between group attrition will be conducted (i.e., differences in baseline characteristics of those that remain in study and those that drop out e.g., *x2*, *t*-test, Mann-Whitney U).

*Intent-to-treat (ITT)*. All analyses will be conducted with an ITT approach and missing values on follow-up data will be imputed using the maximum likelihood (ML) approach.

*Sensitivity analysis*. All results will be investigated through sensitivity analysis for their robustness to assumptions and method choices made during the course of the study (e.g., results with imputation vs results without imputation, changes in resource use and cost data).

*RQ1*. The relative effectiveness of My Choice–My Way! and US will be assessed by analyzing within group and between-group changes on participant self-reported and register data after T2 and again after T3 data collection using e.g., ANOVA, ANCOVA depending on final data characteristics.

*RQ2*. Participant characteristics measured at T1 (e.g., gender, age, type of placement) to will be analyzed (e.g., regression-based moderation analysis, ANCOVA depending on final data characteristics) for their moderating effect on changes in self-reported and register data collected at T2 and T3.

*RQ3*. Service provider reported implementation measures (i.e., acceptability, appropriateness, feasibility) and fidelity scores from the systematic session observations will be analyzed (e.g., regression-based moderation analysis, ANCOVA depending on final data characteristics) for their moderating effect on changes in participant self-reported and register data collected at T2 and T3.

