#### Aim 3 statistical methods

*RQ7*. Fidelity ratings from the systematic session observation at T2 will be compared across My Choice–My Way! groups to investigate differences in implementation quality (e.g., independent samples t-test, Mann-Whitney U depending on final data characteristics).

*RQ8*. Fidelity measures collected from My Choice–My Way! T3 will be compared (e.g., ANOVA) for significant differences between groups.

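### Aim 3 labels its youth-outcome comparison by implementation support as posttest, although support is not described as randomised and T1 scores on the repeated scales are available for adjustment

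*Protocol article*

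**What the plan says.** - **Trial design, Design Aim 3:** a "Posttest comparison study comparing implementation and youth level outcomes for organizations engaged in implementation support with organizations not receiving implementation support". One label covers both implementation outcomes and youth-level outcomes.
- **Trial design, Design Aim 1:** the effectiveness comparison is planned "with dependent pre-, post- and follow-up measures". The article therefore separates pre/post designs from posttest designs, and puts the Aim 3 youth outcomes under posttest.
- **Data collection methods:** youth answer the questionnaire three times: "First, pre-test measurements (T1), directly following the informed consent procedure but prior to program start", then at T2 and T3.
- **Aim 1 statistical methods:** "Baseline differences on background and outcome variables between groups at T1 (due to the absence of randomization) will be investigated", and "Any identified differences will be statistically controlled for in between group analyses". Both sentences stand under Aim 1.
- **Aim 3 statistical methods:** fidelity ratings "will be compared across My Choice–My Way! groups to investigate differences in implementation quality" (RQ7), and fidelity measures are compared at T3 (RQ8). No youth-outcome analysis is listed.
- **Project novelty:** "this project will experimentally test the extent to which implementation support impacts fidelity, sustainability and client outcomes".
- **Allocation:** "the research team will not manipulate the normal operating procedures of the participating municipalities/organizations". Trial design calls the study quasi-experimental with natural controls.

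**The concern.** A posttest comparison is natural for fidelity, which has no value before the programme starts. The same reason does not apply to the youth scales in the repeated questionnaire, because the plan already obtains a T1 score on them.

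Two things are at stake. First, youth in supported and unsupported organisations may differ at T1, since nothing suggests that support was randomised. Some of that difference persists to T2 and T3 and would be read as an effect of implementation support on clients, a claim that Project novelty calls experimental. Second, leaving out a correlated T1 score wastes precision in a comparison that, as RQ7 is worded, lies within the My Choice–My Way! arm and so uses about half the sample.

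**Working it through.** **Plan's own figures.** The article gives no sample size or power for Aim 3. Its 124 completers and 85% power belong to the Aim 1 repeated-measures ANOVA and do not carry over. Only the recruitment figures are used: 80 per arm less 20% is 80 × 0.8 = 64 completers in the My Choice–My Way! arm.

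**Assumptions (not in the article).**
- Split by support 32/32, with 21/43 as a variant.
- T1–T2 correlation ρ = 0.3, 0.5 or 0.7.
- True difference d = 0.5 SD, taken from the plan's medium f = .25 (for two groups, d = 2f).
- Two-sided alpha .05, and no clustering at first.

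**Power.** The standard error of the posttest difference in SD units is √(1/32 + 1/32) = 0.25. The noncentrality is 0.5/0.25 = 2.0 at posttest only and 2.0/√(1 − ρ²) with T1 as covariate.

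| | Noncentrality | Power |
|---|---|---|
| Posttest only | 2.00 | 50% |
| T1-adjusted, ρ = 0.3 | 2.10 | 54% |
| T1-adjusted, ρ = 0.5 | 2.31 | 62% |
| T1-adjusted, ρ = 0.7 | 2.80 | 79% |

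With a 21/43 split and ρ = 0.5, the figures are 46% and 57%.

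**False positives at posttest only, with no true effect.** If a T1 gap of D persists only through the T1–T2 correlation, the expected T2 difference is ρD and the noncentrality is ρD/0.25.

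| T1 gap D | Spurious difference ρD (ρ = 0.3 / 0.5 / 0.7) | False-positive rate |
|---|---|---|
| 0.3 SD | 0.09 / 0.15 / 0.21 SD | 6% / 9% / 13% |
| 0.5 SD | 0.15 / 0.25 / 0.35 SD | 9% / 17% / 28% |

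In this model the T1-adjusted test holds about 5%, but only because T1 is then the sole source of the group difference.

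**If the gap is stable (same D at T1 and T2).** At posttest only the whole gap remains: noncentrality 0.3/0.25 = 1.2 or 0.5/0.25 = 2.0, so 22% or 50% false positives. T1 adjustment leaves a bias of (1 − ρ)D. Simulation at 32/32 gives about 8–14% false positives for 0.3 SD and 13–28% for 0.5 SD over ρ = 0.7 down to 0.3. That is better than posttest only, but not 5%.

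**Clustering.** If youth are nested in the 12 organisations of this arm and the model ignores it, the T1-adjusted test rejects about 7–10% at an intraclass correlation of 0.05 and 10–13% at 0.10 (simulation with the gaps above).

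**Would the Aim 1 baseline rule repair this if extended to Aim 3?** Only partly, since it acts on identified differences. At 32/32 a t-test detects a 0.3 SD T1 gap with noncentrality 1.2, that is, 22% of the time. About 78% of such gaps would pass unadjusted.

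**The case against.** The strongest reply is that the article never says the comparison is unadjusted. Posttest is one word in a one-sentence design label. The same word marks the timing of the interviews in Aims 4 and 5, and a comparison made at posttest can still carry a T1 covariate. The full protocol or analysis plan may supply one. This stands in part: a reader might infer that the article prescribes an unadjusted analysis, and it does not. What remains is that the label contrasts with the pre/post design for Aim 1, the baseline rule is confined to Aim 1, and the Aim 3 methods offer nothing else. A later plan that adds T1 would need this label corrected.

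Three further replies hold and limit the point:

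- H3, H4, RQ7 and RQ8 name only fidelity and sustainability, so no Aim 3 hypothesis rests on the youth comparison. Design Aim 3 and Project novelty nevertheless commit to it.
- Design Aim 3 does not name its youth outcomes. The CSQ-8 rates services already received and can have no T1 value, so adjustment for the same measure is impossible there.
- The split, the correlation, the baseline gap and the use of d = 0.5 for this comparison are all assumed.

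**Conclusion.** The point holds as a low-cost improvement to a stated design, not as proof of a wrong analysis. On the natural reading of Design Aim 3, T1 differences between non-randomised groups enter the youth contrasts, and power falls from 54–79% with T1 adjustment to 50% without it. With no true effect, false positives are about 6–13% for a 0.3 SD gap and 9–28% for a 0.5 SD gap. These figures assume 32/32 completers, d = 0.5, ρ between 0.3 and 0.7, and no clustering. The direction does not depend on the exact values as long as T1 and T2 scores are clearly positively correlated.

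Two stronger readings are tempting but unsupported. One is that any T1 gap counts in full as an effect of support. Only ρ times the gap carries over if it persists through the T1–T2 correlation, and all of it only if the group difference is stable; the documents do not say which applies. The other is that T1 adjustment restores a 5% error rate. Stable group differences, organisation-level confounding and clustering in 12 organisations all remain after adjustment.

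**What to change.** 1. In Design Aim 3, keep the posttest label for implementation outcomes and for youth measures with no T1 value, such as the CSQ-8.
2. For youth scales measured at T1, state in Design Aim 3 and in the Aim 3 statistical methods that the T2 and T3 comparisons include the youth's own T1 score on that scale as a covariate, whether or not a baseline difference is identified.
3. Describe the comparison by implementation support on these outcomes as secondary and non-randomised, and acknowledge that organisation-level differences and clustering are not removed by T1 adjustment.
4. Bring the Project novelty wording about an experimental test into line with the quasi-experimental design in Trial design.

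The cost is wording and one covariate per model. T1 scores are already planned for every participating youth, so no further data or participants are needed.

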### Methods

This research project will be conducted in Sweden. The project has at its core the goal of informing practice about how work with implementation and intervention development can occur in order to benefit clients. In addition, we place a high value on keeping the work scientifically relevant and of high quality. Due to this, the project has an ambitious and complex data collection and analysis strategy using qualitative, quantitative and multiple informant methods.

### Study setting

This is a multicenter research project that will be conducted at a total of 21 research sites throughout Sweden. Organizations have naturally self-selected to either implement My Choice–My way! (*n* = 12) or to continue providing Usual Services (US, *n* = 9). All twelve organizations that implement My Choice—My Way! are part of the Swedish social services, although some are public and others private providers of services to youth. The nine organizations that constitute the control group and provide US are various organizations that provide support for the target group either within the Swedish social services or as a part of civil society. A list of study sites can be obtained from the first author of this protocol.

### Eligibility criteria

The project has two target groups: youth and service providers.

#### Youth participants

All youth in Sweden aged 15 years or older living in out-of-home care and placed by participating organizations, or who self-refer to the services provided by participating organizations, will be eligible for participation and invited to participate. Additional inclusion criteria for participating in My Choice–My Way!: the youth have the ability to spend periods of time outside of placement (i.e., institutional placement) without incident as determined by referring social worker. My Choice–My Way! should never be provided as a replacement for existing treatment services within the organization. Although our goal is to open inclusion to all youth aged 15 or older in out-of-home care, certain unforeseen characteristics may necessitate development of exclusion criteria (e.g., presence of severe intellectual disability).

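### Eligibility and site type differ by arm under the stated rules, and the planned control for identified T1 differences does not clearly cover either

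*Protocol article*

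**What the plan says.** **Eligibility (Youth participants).** The common rule covers youth aged 15 or older in out-of-home care who are placed by a participating organisation, "or who self-refer to the services provided by participating organizations, will be eligible for participation and invited to participate". A further criterion then applies to the intervention arm alone: "the youth have the ability to spend periods of time outside of placement (i.e., institutional placement) without incident as determined by referring social worker". No equivalent is stated for US. The section also leaves room for exclusion criteria to be developed later.

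**Sites (Study setting).** Organisations chose for themselves whether to implement the programme. The twelve intervention organisations "are part of the Swedish social services, although some are public and others private providers of services to youth". The nine control organisations are "various organizations that provide support for the target group either within the Swedish social services or as a part of civil society". The split among the nine is not given.

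**Allocation.** "This study will follow the natural assignment of youth to condition".

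**Analysis (Aim 1 statistical methods).** "Baseline differences on background and outcome variables between groups at T1 (due to the absence of randomization) will be investigated". The rule that follows is: "Any identified differences will be statistically controlled for in between group analyses". Under RQ2, gender, age and type of placement are given as examples of characteristics measured at T1.

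**The concern.** A quasi-experiment with natural assignment is expected to have non-equivalent arms, and the article says so. The issue here is narrower: a written rule screens one arm, and not the other, on a trait that is probably prognostic. Managing time outside placement without incident plausibly relates to self-efficacy and resilience (primary outcomes) and to later criminality and hospital care (register outcomes listed under Other outcomes). H1 predicts gains for My Choice relative to US. If youth who would fail the criterion stay in the US arm only, part of an apparent benefit in RQ1 could come from the eligibility rule.

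Site type is a second structural difference. Youth served by civil-society organisations can appear only in the control arm, so they have no counterpart among My Choice youth.

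**Working it through.** The plan gives no figure on this point to reproduce. The check is a reading of the text, followed by an illustration with assumed inputs.

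**1. Does the planned adjustment reach the two differences?**

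| Difference | My Choice | US | Covered by control for identified T1 differences? |
|---|---|---|---|
| Without-incident judgement | Required, made by referring social worker | Not stated | Only through proxies (type of placement, T1 outcome scores), unless the judgement is also recorded for US youth, which the article does not show |
| Civil-society site | 0 of 12 | Some of 9, number not given | Not by covariates: no intervention site is in civil society, so there is no overlap. Restriction to social-service sites can address it if enough US sites qualify |

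**2. Unadjusted size of the screening difference.** Let q be the share of US youth who would fail the criterion and delta their outcome deficit in SD. Neither is in the documents. The shift in the US mean is q × delta.

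- Low end: 0.1 × 0.2 = 0.02 SD
- Middle: 0.2 × 0.5 = 0.10 SD
- High end: 0.4 × 0.8 = 0.32 SD

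With 80 recruited per arm and 20% dropout (Sample size), 80 × 0.8 = 64 complete per arm. The standard error of a difference in SD units is √(2/64) = 0.177. For a two-sided 5% z-test, unadjusted and ignoring clustering, the false-positive rate becomes 5.1% at 0.02 SD, 8.7% at 0.10 SD and 44% at 0.32 SD.

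**3. After baseline adjustment.** If the deficit is stable over time and the correlation of baseline with follow-up is rho, ANCOVA leaves about q × delta × (1 − rho), and a change-score analysis leaves about zero. With rho assumed at 0.5–0.7:

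- 0.02 SD becomes 0.006–0.01 SD
- 0.10 SD becomes 0.03–0.05 SD
- 0.32 SD becomes 0.10–0.16 SD

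**4. Does the adjustment always apply?** It is triggered by a difference being identified. If that means p < 0.05 (an assumption; the article does not define it), the standard error at T1 with 80 per arm is √(2/80) = 0.158. A true baseline difference of 0.10 SD is then detected about 10% of the time, and one of 0.20 SD about 24%. Differences of this size would often go uncontrolled.

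**5. Cost of restricting the comparison.** If only US youth who meet the criterion are kept, completers number 64 + 64 × (1 − q): 121.6 at q = 0.1, 115.2 at q = 0.2 and 102.4 at q = 0.4. The stated minimum is 124. The total falls below it once 128 − 64q < 124, that is q > 0.0625.

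**The case against.** The strongest reply is that the article declares a quasi-experimental design and already plans to control for T1 differences. Baseline self-efficacy, resilience and need satisfaction are the T1 values of the primary outcomes, so a lower-functioning US arm can show up there and be adjusted for. Type of placement is measured. The list of T1 characteristics is given as examples, so the judgement may well be recorded. This stands to the extent that a reader might infer that the imbalance cannot be adjusted, or that the judgement is not collected for US youth. The documents support neither inference. They show only that the planned control does not clearly cover the two differences.

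A reader might also infer that both differences favour the intervention. For site type nothing supports a direction: civil-society services may attract motivated, self-referred youth, which would favour control. For the screening rule the inference is plausible but not certain. H1 concerns gains, and youth starting lower may have more room to improve.

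The reach of the criterion is uncertain as well. Its parenthesis points to institutional placements, while the US examples in the article are group homes, supported apartments and mentoring. The share of US youth who would fail it could be near zero.

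What the reply does not answer is that adjustment depends on a difference being identified, that baseline scores correct for differences in level but not in expected course, and that covariates cannot separate civil-society status from arm.

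**Conclusion.** The point holds in a limited form. Eligibility and site type differ by arm under the stated rules, beyond what natural assignment alone produces, and the planned control for identified T1 differences may remove part of this but does not clearly cover either. The screening rule plausibly selects lower-risk youth into My Choice; the effect of site type has no known direction.

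The size cannot be derived from the documents. Under the assumed ranges (q 0.1–0.4, delta 0.2–0.8 SD) the unadjusted bias from screening is about 0.02–0.32 SD. It is smaller after baseline adjustment: at most about 0.16 SD by ANCOVA at rho = 0.5 if the deficit is stable. It could be close to zero if few US youth would fail the criterion. These figures illustrate what is at stake and are not estimates of the bias in this trial. The matter deserves correction because it bears on RQ1, the main effectiveness comparison, and the remedy is cheap.

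**What to change.** 1. Record the same yes/no judgement at T1 for US youth, made by the responsible worker where there is no referring social worker (for example, for self-referred youth).
2. Prespecify for RQ1, alongside the all-youth analysis, a comparison limited to youth in both arms who meet the criterion.
3. Prespecify a sensitivity analysis limited to US sites within the social services, and report how many of the nine qualify.
4. State that any exclusion criterion developed later applies to both arms.
5. Where the judgement was not recorded for youth already enrolled, treat it as missing and adjust for type of placement. Placement status should not be substituted for the judgement, because it does not measure it.

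**Cost.** One extra item at T1 and two analysis-set definitions. The restricted US sets are smaller and less precise, and the total in the criterion-based comparison falls below the 124 completers in the sample size section once more than about 6% of US youth fail the criterion. That is why it should stand beside the all-youth analysis and not replace it.
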